### Secondary outcomes

#### Depressive symptoms

The Edinburgh Postnatal Depression Scale (EPDS)
[31] is a 10 item depression scale developed for women in the postpartum period. Item response varies from 0 to 3. Total score range is 0–30. Cronbach’s alpha was 0.82 in the Dutch paper-pencil version
[32]. As the EPDS is not well validated as a screenings instrument in the antepartum period we will not use it as our primary outcome
[33]. We will use the EPDS as a secondary measuring instrument for comparison as this scale is widely used in this target population.

### Health care utilization

We will monitor uptake of health care, during the whole study period with the TiC-P
[34].We will include all health care utilization of the mother (e.g. visits to general practitioner, to mental health care, to gynaecologist, hospital admissions etc.), as well for the new-born (e.g. additional visits from the midwife or to the child health centre, to the general practitioner and/or the paediatrician) irrespective of the cause or reason for using the service.

### Productivity losses

We will also monitor possible productivity losses. We will register the duration of the maternity leave, frequency and duration of sick leave from work (absenteeism) and the extent a women has worked but less efficient (presenteeism). This will be measured with the SF-HLQ which is incorporated within the TIC-P
[34].

### Quality of life

Quality of life is assessed with the Euroqol
[34–37]. This is self report questionnaire which measures quality of life and consists of 5 health state dimensions (pain/discomfort, depression/anxiety, mobility, self-care and usual activity) giving an indication of the own health state. The value that the individual or the society may place on a particular health state is expressed in a utility score. This utility score varies by a number between 0 (worst imaginable condition: death) and 1 (perfect health). In the Netherlands the tariff of valuation to determine the utility score is used to calculate quality-adjusted life years (QALYs) by multiplying the utility score with the amount of years the health state exists.

### Demographics

We will assess gender, age, marital status, number and ages of other children, education, profession and ethnicity.

### Assessments

All assessments are based on self-report and will take place online (Table 
1). We will measure at baseline (T0), 10 weeks later (although it is possible to finish the intervention in 6 weeks we know that there will be some people who need more time. To ensure that the post-test assessment takes place after completing the intervention we will perform the post-test assessments after 10 weeks.), when the intervention group has finished the intervention (T1), 4 weeks before the expected day of birth (in order to registrate symptoms of relapse (T2), and 6 weeks after delivery (T3). Participants starting the intervention after 24 weeks of pregnancy will not be assessed at T2, since the time period between T1 and T2 will be too small.

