**Methods/design:**

We will investigate the effectiveness of a 6 week internet-based self-help problem solving treatment (PST) for affective symptoms in pregnancy. We aim to include 286 women with mild to severe affective symptoms who will be randomly assigned to the internet-based intervention or a waiting list control group. Primary outcome measures are affective symptoms and the perinatal outcome. Secondary outcome measures are quality of life, and economic costs. All assessments are based on self-report and will take place at baseline (T0), 10 weeks later (after completion of the intervention (T1), 4 weeks before the expected day of birth (T2), and 6 weeks after delivery (T3). The control group will be measured at the same moments in time. Analysis will be based on the intention-to-treat principle.

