**Flowchart selection, inclusion, intervention and measurement.**

### Inclusion and exclusion criteria

We will include participants who are at risk for developing postpartum depression. More specifically, we will include participants of 18 years and older, who are pregnant but are at least 10 weeks before the expected delivery date, and have at least mild symptoms of depression or anxiety. Symptoms of depression are measured with the Center for Epidemiological Studies Depression scale (CES-D) and symptoms of anxiety with the Hospital Anxiety and Depression Scale- Anxiety subscale (HADS-A)
[20, 21]. Patients are eligible if they score at least 16 on the CESD and/or 8 on the HADS-A. Participants who indicate that they either intend to harm themselves or want to attempt suicide (as assessed by one question of the Web Screening Questionnaire (WSQ)
[22]) will be excluded. They are advised to consult their general practitioner to obtain more tailored care. Receiving psychiatric treatment including psychotherapy or the use of psychopharmacological agents such as antidepressants is allowed. Any additional treatments will be monitored through patients self-report at the end of study.

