### Sample size and statistical analysis

Analyses will be conducted according to intention-to-treat as well as per protocol principle. To study differences between the conditions we will use linear mixed models with symptoms of depression and anxiety as dependent variables, time indicators and treatment dummy as predictors, since these types of models account for drop out over time. We will compute both within group effect sizes and between group effect sizes. The within group effect sizes are standardized differences of (predicted) means of the follow up scores and baseline scores. The between group effect sizes concern differences between within group effect sizes. We assume that the between group effect size (Cohen’s d) at the end of the study will be at least 0.40, because this has been demonstrated in a meta-analysis on supported internet treatments in general
[13] and in previous studies using the same problem solving internet treatment
[19, 25]. Using an alpha of 0.05 (two-tailed), a statistical power (1-bèta) of 0.80, and an attrition rate of 30%
[19] we need 143 respondents in each arm. All analyses will be conducted using SPSS for Windows, version 20 and STATA 10.0.

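### The T2 omission rule hangs on starting the intervention, which controls do not do before T3, and the stated model leaves out the gestational age that decides who has a T2

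*Protocol article*

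**What the plan says.** Four parts of the protocol article bear on this.

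- **Entry.** Under Inclusion and exclusion criteria, eligible women "are at least 10 weeks before the expected delivery date".
- **Visits.** Under Assessments, T1 is fixed by time since baseline ("we will perform the post-test assessments after 10 weeks") and T2 by the due date ("4 weeks before the expected day of birth"). T2 is then dropped for some women: "Participants starting the intervention after 24 weeks of pregnancy will not be assessed at T2", the reason being "since the time period between T1 and T2 will be too small".
- **Arms.** Study design and Control group both place the controls' access to the intervention at six weeks postpartum, after follow-up ends. The Abstract (Methods/design) says: "The control group will be measured at the same moments in time". Table 1 gives a single schedule and does not separate the arms.
- **Model.** Sample size and statistical analysis specifies linear mixed models with "time indicators and treatment dummy as predictors", chosen because such models are said to deal with drop-out. Gestational age is not among these predictors, nor among the variables listed under Demographics, although eligibility and the T2 date cannot be worked out without the due date.

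The Background names the end of pregnancy as one of the three time points of the first aim, so T2 is not incidental.

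**The concern.** The rule refers to an event that only the intervention arm can have during follow-up, and one that happens after randomisation. A woman randomised at 23 weeks who begins at 25 would lose T2; a control randomised at 23 weeks would not. Applied as written, the rule makes the two arms' T2 samples differ in gestational age at entry.

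Even on a common schedule, a T2 that was never scheduled is not drop-out. It is set by gestational age at entry, and the stated model does not contain that variable. The T2 means would then describe early entrants while being presented as those of the whole trial.

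Finally, T1 follows baseline by a fixed interval with no provision for delivery. One T1 indicator can therefore cover a mid-pregnancy score for one woman and a postpartum score for another.

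**Working it through.** **Plan's own figure.** For d = 0.40, two-sided alpha 0.05 and power 0.80, the two-sample t-test needs 99.08, so 100 per arm. 100 / 0.70 = 142.9, so 143 per arm. The stated number is reproduced. It is set for the end of the study.

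**Visit timing.** Assume a due date at 40 weeks. Latest entry = 40 - 10 = week 30. T1 = entry + 10. T2 = 40 - 4 = week 36.

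| Entry (week) | T1 (week) | T2 date minus T1 (weeks) |
|---|---|---|
| 20 | 30 | 6 |
| 24 | 34 | 2 |
| 26 | 36 | 0 |
| 28 | 38 | -2 |
| 30 | 40 | -4 |

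The 24-week cut-off removes T2 before the two visits collide. It does nothing about T1 and delivery. Assume delivery is normally distributed with mean 39.5 to 40 weeks and SD 1.3 to 2.0. The chance that T1 falls after delivery is then below 1% for entry at 24 weeks, 6 to 23% at 28, 22 to 40% at 29 and 50 to 65% at 30.

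**Bias in the T2 contrast.** Assumptions: entry uniform over weeks 10 to 30, true T2 effect -0.40 score units, T0 and T1 observed for all, and T2 scores shifting by 0.2 or 0.4 units per 10 weeks of gestation at entry. Late share = (30 - 24)/20 = 30%. Mean entry is week 20 overall and week 17 among those at or before 24, a difference of -0.3 in units of 10 weeks.

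- *Rule in one arm only.* Expected bias = slope x (-0.3): 0.2 gives -0.06 and 0.4 gives -0.12, so estimates of -0.46 and -0.52. Simulation with 400,000 women per scenario gave -0.459 and -0.525. With a zero slope there was no bias (-0.394). Adding gestational age and its product with arm returned about -0.40.
- *Rule in both arms, same effect at all gestations.* Simulated estimates without gestational age were -0.405, -0.403 and -0.401 for slopes 0, 0.2 and 0.4: no bias.
- *Rule in both arms, effect changing by 0.2 per 10 weeks.* Expected -0.40 + 0.2 x (-0.3) = -0.46; simulated -0.454 to -0.456. This is the effect in early entrants, not in all randomised women.

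**Precision at T2.** The documents give no late-entry share. If 20, 30 or 40% enter late and 100 per arm would otherwise be observed, 80, 70 or 60 remain. For a contrast using T2 completers only, the standard error grows by 1/sqrt(0.8) = 1.12, 1/sqrt(0.7) = 1.20 or 1/sqrt(0.6) = 1.29. The mixed model borrows from the other visits, so these are upper figures.

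**The case against.** The best reply is that a common schedule was plainly meant. The Abstract's sentence on the control group and the undivided Table 1 point that way, with starting the intervention as shorthand for entering the trial. Missingness would then depend on a pre-randomisation characteristic that randomisation balances, and the simulation shows no bias without effect modification. This largely stands. A reader might infer from the Assessments wording that controls are in fact assessed at T2 while late intervention women are not; the documents do not show that. They show wording that no control can satisfy beside a sentence that implies both arms are treated alike.

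A reader might also infer a power shortfall at T2. With the assumed late shares of 20, 30 or 40%, completers-only power for d = 0.40 would be about 0.72, 0.66 or 0.59. But the protocol set 0.80 for the end of the study and promised none for T2, and the late share is a guess. No shortfall against a stated target follows.

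Nor is it a fault that T1 would follow the T2 date for entry after week 26: the 24-week rule already removes T2 for those women. Postpartum T1 scores are confined to the latest entrants, and on a common schedule both arms share them.

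Last, covariates and visit windows are often left to a fuller document. That is fair for detail, but here the article itself states the predictors and the omission rule, and the rule contradicts another statement in the article.

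**Conclusion.** The point holds in a limited form. The wording of the T2 rule conflicts with the statement that both arms are measured at the same moments, and the two must be reconciled. If the literal rule were followed, the T2 contrast could be off by about 0.06 to 0.13 units on a true -0.40, under the assumed slopes and uniform entry. If the rule applies to both arms, the cost is lost precision and a T2 result that rests on women entering at or before 24 weeks; bias for the whole randomised population arises only if the effect varies with gestation at entry (about 0.06 under the assumed interaction). T1 at about week 40 for entry at week 30 follows from the eligibility limit and an assumed 40-week due date; how many T1 scores are postpartum depends on the unknown entry distribution. Neither a one-arm omission nor an underpowered trial is shown.

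**What to change.** 1. Define the T2 rule by gestational age at randomisation, identically in both arms, and align the Assessments wording with the Abstract.
2. Add gestational age at randomisation and its interaction with the time indicators to the mixed models.
3. Report the T2 contrast as applying to women randomised at or before 24 weeks, with its own n. No T2 scores exist beyond that point, so a model-based T2 estimate for later entrants would be extrapolation.
4. Record whether each T1 was completed before or after delivery, and run a sensitivity analysis excluding postpartum T1 scores. It should stay a sensitivity analysis, because time of delivery follows randomisation and relates to the perinatal outcomes.

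The cost is small: a change of wording, a baseline value already needed for eligibility and for scheduling T2, and a few extra model parameters (with a linear term, one main effect and three time interactions per outcome). No assessment is added and 143 per arm does not change.

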**Table 1 Tab1:** **Assessment time table**

	T0	T1	T2	T3
CES-D	X	X	X	X
HADS	X	X	X	X
WSQ	X			X
EPDS	X	X	X	X
TiC-P	X	X	X	X
Euroqol	X	X	X	X
Demographic variables	X			
Delivery outcome				X

### Sample size and statistical analysis

Analyses will be conducted according to intention-to-treat as well as per protocol principle. To study differences between the conditions we will use linear mixed models with symptoms of depression and anxiety as dependent variables, time indicators and treatment dummy as predictors, since these types of models account for drop out over time. We will compute both within group effect sizes and between group effect sizes. The within group effect sizes are standardized differences of (predicted) means of the follow up scores and baseline scores. The between group effect sizes concern differences between within group effect sizes. We assume that the between group effect size (Cohen’s d) at the end of the study will be at least 0.40, because this has been demonstrated in a meta-analysis on supported internet treatments in general
[13] and in previous studies using the same problem solving internet treatment
[19, 25]. Using an alpha of 0.05 (two-tailed), a statistical power (1-bèta) of 0.80, and an attrition rate of 30%
[19] we need 143 respondents in each arm. All analyses will be conducted using SPSS for Windows, version 20 and STATA 10.0.

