### Recruitment

Participants will be recruited from the general Dutch population by means of banners on internet websites and advertisements in newspapers and magazines for pregnant women. These banners and advertisements refer to our study website. The website provides general information about the study and women can register online. All registered women will then be informed in more detail. They will also receive an informed consent form and a link to a baseline questionnaire. Only women who return a signed informed consent, complete the online baseline questionnaire, meet inclusion criteria and do not meet exclusion criteria will be included and randomized. Participants with very severe depressive or anxiety symptoms (CESD ≥ 25 or HADS-A ≥ 12) will be advised to contact their general practitioner as well, since the possibility exists that they need additional treatment. They will not be excluded since there exists evidence that the intervention is also helpful in case of severe depressive symptoms
[23, 24].

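### The symptom models use no baseline adjustment although T0 scores exist for every randomised woman; at an assumed correlation of 0.5 and equal SDs this forgoes about 7 points of power

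*Protocol article*

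**What the plan says.** The section on sample size and statistical analysis of the protocol article plans "linear mixed models with symptoms of depression and anxiety as dependent variables, time indicators and treatment dummy as predictors". It then defines the effect measures: "The within group effect sizes are standardized differences of (predicted) means of the follow up scores and baseline scores", and the between-group effect is one arm's within-group effect size minus the other's. No baseline covariate is named, and nothing says that the two arms share a common mean at T0.

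The baseline scores are available. Table 1 (Assessment time table) lists the CES-D and HADS at T0, T1, T2 and T3. The Recruitment section makes a completed baseline questionnaire a condition of randomisation: "Only women who return a signed informed consent, complete the online baseline questionnaire, meet inclusion criteria".

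The sample size is a plain two-group comparison that uses no baseline correlation. Its inputs are a Cohen's d that "at the end of the study will be at least 0.40", "Using an alpha of 0.05 (two-tailed"), "a statistical power (1-bèta) of 0.80" and "an attrition rate of 30"%, leading to "we need 143 respondents in each arm".

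**The concern.** A difference of changes subtracts the whole baseline score from each woman's follow-up score, whereas only a fraction of the baseline score carries forward to follow-up. Unless that fraction is one, the contrast has a larger variance than one that adjusts for baseline. The symptom scores are primary outcomes, and the covariate that would sharpen the comparison is already in hand for everyone randomised. At stake is precision on the primary symptom comparison, and some protection of the planned power if the baseline-to-follow-up correlation proves low.

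The wording raises a second difficulty. The named predictors include no treatment-by-time term. With time indicators and one constant treatment dummy, the predicted change is the same in both arms, so that model cannot produce the between-group effect that the same paragraph defines. If T0 is among the modelled outcomes, the treatment coefficient averages over a time point at which no effect can exist.

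**Working it through.** **Inputs from the protocol article:** d = 0.40, two-sided alpha 0.05, power 0.80, attrition 30%, 143 per arm, 1:1 allocation.

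**Assumptions, because the documents give no values:** baseline-to-follow-up correlation ρ, shown from 0.4 to 0.7; equal SDs at T0 and follow-up, relaxed in step 4; drop-out at random.

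**1. The plan's own figure.** Noncentral-t power for d = 0.40 is 0.7997 with 99 per arm and 0.804 with 100 per arm, so 100 are needed. Then 100 / 0.70 = 142.9, which rounds up to 143. The stated figure reproduces.

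**2. Standard errors of the effect at follow-up, in follow-up SD units** (T0 on 143 per arm, follow-up on 100 per arm):

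- Mixed model with T0 means free by arm and treatment-by-time terms: √(2[(1−ρ²)/100 + (1−ρ)²/143])
- Baseline-adjusted: √(2(1−ρ²)/100)

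At ρ = 0.5 the first is √(2[0.0075 + 0.00175]) = 0.136 and the second is √(2 × 0.0075) = 0.122. The adjusted variance is about 19% smaller.

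**3. Power at d = 0.40, equal SDs** (noncentral t):

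| ρ | T0 means free | Baseline-adjusted | Gain (points) |
|---|---|---|---|
| 0.4 | 0.77 | 0.87 | 10 |
| 0.5 | 0.83 | 0.90 | 7 |
| 0.6 | 0.90 | 0.94 | 4 |
| 0.7 | 0.96 | 0.98 | 1.5 |

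These figures treat the 30% as lost before T1. With gradual loss of 10%, 20% and 30% at T1, T2 and T3 under compound symmetry, power at ρ = 0.5 is 0.846 against 0.913, a gap of 6.7 points.

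**4. Unequal SDs.** Eligibility requires at least 16 on the CES-D and/or 8 on the HADS-A, which may narrow the spread at T0. Let the T0 SD be k times the follow-up SD. The free-means standard error becomes √(2[(1−ρ²)/100 + (ρ−k)²/143]), and the adjusted one does not change. At ρ = 0.5, where adjusted power is 0.901:

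| k | T0 means free | Gain (points) |
|---|---|---|
| 1.0 | 0.833 | 6.8 |
| 0.9 | 0.858 | 4.3 |
| 0.8 | 0.877 | 2.4 |
| 0.7 | 0.891 | 1.1 |

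This table holds ρ fixed. Selection on T0 would normally lower ρ as well and leave the regression slope unchanged. Take a slope of 0.5, an unselected follow-up variance of 1 and a T0 SD cut to 0.7. The follow-up variance is then 0.75 + 0.25 × 0.49 = 0.8725 (SD 0.934), ρ = 0.35/0.934 ≈ 0.37 and k = 0.7/0.934 ≈ 0.75. Power is about 0.82 free against 0.86 adjusted, a gain of about 4 points.

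**5. The literal model: one treatment dummy, T0 to T3 as outcomes.** Assume ρ = 0.5, compound symmetry, a true effect of 0 at T0 and 0.40 at each follow-up, and 30% missing at T1 to T3. The treatment coefficient then estimates about 0.237 with a standard error of 0.099. The ratio is 2.39, and power is Φ(2.39 − 1.96) ≈ 0.66. With gradual loss of 10%, 20% and 30%, the effect is about 0.27 and power about 0.79.

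**The case against.** The strongest reply is that one sentence in a condensed article does not fix a model. It gives no coding, covariance structure or T0 constraint, and an analysis plan that is not shown could supply them. The effect definition would also fit a model with a common T0 mean, because there the difference in predicted changes is the baseline-adjusted difference. This stands in part: that T0 means are left free by arm is a reading of the text, not a statement in it. Even so, the article names its predictors and defines its effect, and neither includes an adjustment. The point therefore concerns what is written, not detail left for later.

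Four stronger readings are tempting, and the documents do not support them.

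- **A loss of 10 points at ρ = 0.5.** That figure compares adjustment with change scores in completers only, or with a raw follow-up comparison (each about 0.80 against 0.90). The plan uses neither; it chooses mixed models so as to accommodate drop-out. Against that model the gap is about 7 points.
- **An underpowered trial.** With equal SDs, the change contrast has power 0.83 at ρ = 0.5, above the target. It falls to 0.77 at ρ = 0.4, but at the same correlation with k = 0.8 it is 0.82. A shortfall depends on two quantities that the documents do not give.
- **Bias from chance imbalance at T0.** Under randomisation the change contrast is unbiased, and chance imbalance is already part of the standard errors above. It is not a further cost.
- **The same loss with or without a treatment-by-time term.** Without that term the model does not estimate change at all. The figures in step 3 do not apply to it; those in step 5 do.

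**Conclusion.** The point holds as one of efficiency and clear specification. With the treatment-by-time term that the effect definition needs, the planned contrast is valid and unbiased but less precise than the collected data allow. With equal SDs, the power forgone is about 10 points at ρ = 0.4, 7 at 0.5, 4 at 0.6 and 1.5 at 0.7. At ρ = 0.5 it is about 1 to 4 points if the T0 SD is 0.7 to 0.9 of the follow-up SD. These sizes rest on assumed correlations and SDs. The literal main-effect reading does not rescue the plan, because it dilutes the target effect and has power of about 0.66 under the assumptions in step 5. The change is worth making because it costs almost nothing and the article gives no reason for leaving baseline out.

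**What to change.** In the section on sample size and statistical analysis, specify one of two models for the CES-D and, separately, for the HADS-A:

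1. T1, T2 and T3 as outcomes, with time, treatment, treatment by time and the T0 score of the same scale as a covariate; or
2. T0 to T3 as outcomes, with the T0 mean constrained equal across arms and treatment-by-time terms at T1, T2 and T3.

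The two are close but not identical. The second also keeps women with no follow-up score in the model, whereas in the first they contribute no row. In either case, take the between-group effect at each follow-up from the adjusted difference and report within-group changes as description only.

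The cost is a sentence or two of analysis text and about one degree of freedom. No new data, visits or participants are needed, and 143 per arm can stay.

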In recent years self-help internet programs have become increasingly popular in mental health care. They are based on evidence based psychological treatments. Nowadays, numerous randomised controlled trials are available demonstrating the effectiveness of internet-based self-help interventions for different mental disorders such as depression
[12, 13], anxiety
[14, 15], alcohol
[16], and insomnia
[17]. Various treatment modalities have been applied within these trials, for example Cognitive Behavioural Therapy (CBT) and Problem-Solving Therapy (PST). It has been demonstrated that internet self-help treatments provided with support are more effective than those without any support
[18]. To our best knowledge no evidence is available on self-help internet interventions for depressive and anxiety symptoms in pregnancy.

We will examine the effectiveness of an intervention based on an existing, evidence based internet self help version of PST
[19] compared to a waiting list control condition on (1) the reduction of depressive and anxiety symptoms post intervention, end of pregnancy and 6 weeks postpartum and, (2) the improvement in perinatal outcomes (for example pre-term birth, growth restriction and breastfeeding initiation). We will also (3) determine cost-effectiveness using a societal perspective. We will further explain the intervention in the method section.

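### The listed predictors contain no treatment-by-time term, which conflicts with the plan's own between-group effect size and its time-specific aims

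*Protocol article*

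**What the plan says.** Under Sample size and statistical analysis, the Protocol article states that arm differences will be studied with "linear mixed models with symptoms of depression and anxiety as dependent variables, time indicators and treatment dummy as predictors". The reason given for a mixed model is that it accounts for drop-out. No interaction term is named there or elsewhere in the article.

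The same paragraph then defines the effect measures: "The within group effect sizes are standardized differences of (predicted) means of the follow up scores and baseline scores", followed by "The between group effect sizes concern differences between within group effect sizes". The sample size rests on this between-group measure: "We assume that the between group effect size (Cohen’s d) at the end of the study will be at least 0.40".

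The Background gives the aim as "the reduction of depressive and anxiety symptoms post intervention, end of pregnancy and 6 weeks postpartum". The assessment table has the CES-D and HADS at T0, T1, T2 and T3.

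**The concern.** Taken as a list of model terms, time indicators plus a treatment dummy allow only one arm difference, the same at every visit. Baseline appears to be one of the modelled visits, because predicted baseline means are needed for the within-group effect sizes. Three things follow.

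- The single treatment coefficient averages the follow-up effect with the baseline difference, whose expectation is zero under randomisation.
- The model yields no separate effect at T1, T2 or T3, which are the times named in the aim.
- The change from baseline that the model predicts is the same in both arms, so the plan's own between-group effect size carries no information about treatment.

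An analyst who followed the clause literally would test one quantity while the trial was sized on another.

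**Working it through.** **1. The plan's sample size.** Inputs from the article: d = 0.40, two-sided alpha 0.05, power 0.80, attrition 30%. The t-test calculation gives 99.08, rounded up to 100 per arm, and 100 / 0.7 = 142.9, so 143. (The normal approximation gives 99, and 99 / 0.7 = 141.4, so 142.) The stated "we need 143 respondents in each arm" is reproduced.

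**2. Predicted change under the listed predictors.** Write E[y] = a_t + b × treat. In either arm, predicted change from T0 to visit t is (a_t + b × treat) − (a_0 + b × treat) = a_t − a_0. The arms do not differ, so with a common standardising SD the between-group effect size is 0 at every follow-up. In 60 simulated trials (143 per arm, true effect 0.40, 30% lost after T0, correlation 0.5), the largest absolute difference in predicted change at T3 was 1e-16. The model with treatment-by-time terms gave a mean of 0.42 in magnitude. Standardising each arm by its own baseline SD gave mean 0.004 and SD 0.04, which is noise.

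**3. What the coefficient b estimates.** Assumptions not in the article: effect 0 at T0 and 0.40 at T1 to T3, unit SD, compound symmetry with correlation ρ, and the same drop-out in both arms. If a fraction w_k of women have k visits including T0, the generalised least squares coefficient is

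b = 0.40 × Σ w_k (k − 1)/(1 + (k − 1)ρ) ÷ D, where D = Σ w_k k/(1 + (k − 1)ρ), and SE(b) = √(2/(n D)).

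- Complete data: b = 0.40 × 3/4 = 0.30.
- All 30% lost right after T0, ρ = 0.5: the sum is 0.7 × 3/2.5 = 0.84 and D = 0.7 × 4/2.5 + 0.3 = 1.42, so b = 0.40 × 0.84/1.42 = 0.237. SE = √(2/(143 × 1.42)) = 0.099, and power is 0.66.
- Loss spread evenly (10% before each of T1, T2 and T3), ρ = 0.5: the sum is 0.84 + 0.10 + 0.067 = 1.007 and D = 1.12 + 0.15 + 0.133 + 0.10 = 1.503, so b = 0.268. SE is 0.096 to 0.097, and power is 0.79.

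**4. Range over correlation and drop-out timing** (143 per arm, 30% attrition; pairs are loss all after T0 / spread evenly):

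| ρ | b | Power, test of b | Power, T3 interaction contrast | Power, T3 contrast with common baseline mean |
|---|---|---|---|---|
| 0.3 | 0.249 / 0.273 | 0.80 / 0.89 | 0.72 / 0.72 | 0.84 / 0.85 |
| 0.5 | 0.237 / 0.268 | 0.66 / 0.79 | 0.84 / 0.85 | 0.91 / 0.91 |
| 0.7 | 0.225 / 0.263 | 0.55 / 0.70 | 0.96 / 0.97 | 0.98 / 0.98 |

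Both T3 contrasts have expectation 0.40 throughout.

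**5. An effect that grows.** If the true effects at T0 to T3 are 0, 0.2, 0.3 and 0.4, then b = 0.9/4 = 0.225 with complete data. It is about 0.19 to 0.17 (ρ 0.3 to 0.7) with 30% lost after T0.

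These figures leave out the planned omission of T2 for women who start after 24 weeks. For them baseline has weight 1/3 rather than 1/4, which would dilute b slightly more.

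**The case against.** The strongest reply is that the clause, in a condensed article, lists the variables that enter the model rather than its full formula. It does not say main effects only. The definitions that follow it make sense only if arm-by-time means can differ, so an interaction was probably intended, and the exact formula may stand in a fuller document. An analyst would also notice at once that predicted changes were identical in both arms.

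Much of this stands. A reader might infer that the plan rules out an interaction, or that the trial is bound to report a zero effect size. The article supports neither:

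- Zero requires the additive reading, model-predicted means and a common SD. The word for predicted is in brackets in the definition, and observed means would not give zero.
- T0 as an outcome row is implied, not stated.

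A reader might also infer that power is always lost. At ρ = 0.3 the test of b has 0.80 to 0.89, against 0.72 for the unconstrained T3 interaction contrast.

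The reply does not remove the conflict. The predictors that are stated cannot produce the effect size that is defined in the same paragraph, so this is more than detail left to another document. Falling back on observed means would give up the drop-out handling that is the stated reason for the mixed model.

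**Conclusion.** The concern holds as an internal conflict. The listed predictors do not match the plan's between-group effect size, the 0.40 at study end on which the trial is sized, or the three follow-up times in the aim. Fitted as listed with T0 among the outcomes, the model dilutes a constant true effect of 0.40 to 0.30 with complete data, and to about 0.22 to 0.27 (roughly 56% to 68% of the truth) with 30% attrition. It also makes the effect size from predicted means with a common SD zero.

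The dilution figures rest on assumed compound symmetry, correlations of 0.3 to 0.7 and two drop-out timings, none of which the article gives. The algebra for predicted change needs none of these. At correlation 0.5 the test of the coefficient has power of about 0.66 to 0.79, but the loss of power is not general. The firm harm is to what is estimated and to the effect size reported.

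**What to change.** Add treatment-by-time-indicator terms to the stated model. Preferably constrain the arms to a common baseline mean; using baseline score as a covariate with T1 to T3 as outcomes serves the same purpose. Derive the between-group effect sizes from the model contrasts at T1, T2 and T3, with one common standardising SD, and name the T3 contrast as the one that matches the sample size.

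The cost is a change of wording in the analysis paragraph. No new data or assessments are needed, and 143 per arm is unaffected. Under the assumptions above, the T3 contrast with a common baseline mean has power of 0.84 to 0.98.
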